# The Effect of Group Support Psychotherapy Delivered by Trained Lay Health Workers for Depression Treatment Among People with HIV in Uganda: Protocol of a Pragmatic, Cluster Randomized Trial

**DOI:** 10.2196/resprot.8925

**Published:** 2017-12-11

**Keywords:** cluster randomized trial, group support psychotherapy, lay health workers, depression, persons living with HIV/AIDS, Uganda

## Abstract

**Background:**

There is limited information on the effectiveness of task shifting of mental health services in populations with HIV.

**Objective:**

This trial aims to evaluate the effectiveness of group support psychotherapy delivered by trained lay health workers to persons living with HIV (PLWH) with depression in primary care.

**Methods:**

Thirty eligible primary care health centers across three districts were randomly allocated to have their lay health workers trained to deliver group support psychotherapy (intervention arm) or group HIV education and treatment as usual (control arm) to PLWH with depression. Treated PLWH will be evaluated at baseline, after the end of treatment, and at 6-month intervals thereafter for 2 years. Primary outcomes will be the difference in follow-up proportions of participants with Mini International Neuropsychiatric Interview criteria for major depression and difference in follow-up function scores of participants in the intervention and control arms 6 months after the end of treatment. Secondary outcomes will include measures of self-esteem, posttraumatic stress symptoms, social support, stigma, adherence to antiretroviral therapy, viral load, and number of disability days, asset possession indices, and cost-effectiveness data. Primary and secondary outcomes as well as subgroup analyses will be conducted at the individual level using multilevel random effects regression analyses adjusting for clustering in health centers. A process evaluation using mixed methods to assess acceptability, feasibility, fidelity, causal mediating processes, and contextual influences in the trial will be conducted.

**Results:**

The trial has been approved by the Makerere College of Health Sciences School of Health Sciences Research Ethics Committee, the AIDS Support Organization, and the Uganda National Council of Science and Technology. A data and safety monitoring board has been put in place to monitor trial progress. A total of 1140 persons living with HIV have been recruited to the trial. An analysis of baseline and 6-month data is in progress. The results of this trial will not only be presented at national and international conferences but also submitted for publication in peer-reviewed journals and as a report to the funding agencies.

**Conclusions:**

This cluster randomized trial will provide critical evidence to support culturally sensitive group-based psychotherapy for depression treatment in sub-Saharan Africa. Process evaluation outcomes will provide contextual information that health care and public health stakeholders can use to guide implementation decisions for their particular setting.

**Trial Registration:**

Pan African Clinical Trials Registry (PACTR): 201608001738234; http://www.pactr.org/ATMWeb/ appmanager/atm/atmregistry?dar=true&tNo=PACTR201608001738234 (Archived by WebCite at http://www.webcitation.org/ 6vUAgAQlj)

## Introduction

In the fight against the HIV epidemic over the past three decades, one of the major barriers to universal access to health care needed by persons living with HIV (PLWH) has been a serious shortage of health workers to deliver these interventions [1]. The shortage of well-trained health workers to address the myriad biological, social, and psychological challenges of living with HIV poses a risk for suboptimal HIV treatment outcomes, particularly in sub-Saharan African countries where the burden of HIV and acquired immune deficiency syndrome (AIDS) is greatest [2]. For example, the lack of capacity to provide mental health care such as screening for depression in HIV care programs results in undetected and untreated depression, which impairs the ability to adhere to antiretroviral (ART) medications [3,4]. Affected individuals continue to struggle with poor health, social, and economic outcomes because depression impairs their ability to function in their families, at work, and in their communities [5,6].

The World Health Organization (WHO) HIV treatment guidelines now recognize depression treatment as central to effective HIV treatment programs [7]. This, in turn, has resulted in the development and testing of a number of psychological interventions for depression that can be used in poor resource areas where the gap between the availability and need for mental health services [8-10], known as the “treatment gap,” may be as high as 90% [11]. Unfortunately, accessibility and sustainability of these interventions is impeded by the severe shortage of mental health professionals who can deliver them to affected individuals who need them [12].

Task-shifting approaches, whereby nonspecialist health workers in primary care and community settings are trained to deliver some of the mental health services that were provided solely by specialist mental health professionals, have been recommended by global mental health researchers and practitioners [13] as well as the WHO. The WHO recommends that these task-shifting approaches must use standardized and simplified interventions that can realistically be administered by less highly trained professional health care workers and nonprofessional community members [2]. However, studies describing the implementation of task-shifting approaches in delivery of psychological interventions for PLWH in sub-Saharan Africa are limited.

In a recent review of studies documenting the effectiveness of psychological interventions for PLWH in low- to middle-income countries, none of the studies that met criteria for inclusion in the review demonstrated the use of a task-shifting approach in the delivery of the intervention [14]. In a recent review of studies describing mental health training of health care workers in Africa, only three of the 37 studies reviewed described training of lay health workers (LHWs) [15]. There is a need for information on how a task-shifting approach can be used to make a psychological intervention for depression accessible and sustainable in low-resource settings.

The shifting of mental health‒related tasks from health professionals to LHWs has been repeatedly documented in non-HIV populations [16-19]. However, because mental health has not been integrated into HIV care in sub-Saharan Africa, little is known about the effectiveness of task shifting of mental health‒related services such as depression care. Also, identifying mediators and moderators of intervention response is a critical step in understanding the mediating causal factors as well as for whom and under which conditions an intervention is most beneficial [20]. This knowledge also has important implications for practice, as it can aid in tailoring and modifying interventions so as to be maximally effective for specific target populations.

To address this knowledge gap, we set out to conduct a cluster randomized trial to test the effectiveness of group support psychotherapy (GSP) delivered by trained LHWs. The recommended methodological approach to establish the efficacy of a newly developed therapy such as GSP is to first compare the therapy against a comparison group that omits the unique ingredients of the new therapy while possessing the common factors (eg, therapeutic alliance) in equal measure [21]. Thus, we compared the effects of GSP to those of group HIV education (GHE) delivered by trained LHWs on mild to moderate depression and functioning among PLWH attending primary care health centers in northern Uganda. We hypothesized that compared with the control arm, the proportion of participants that meets the Mini International Neuropsychiatric Interview (MINI) criteria for major depression will be lower and the function scores will be higher in the intervention arm 6 months after the end of treatment.

Secondarily, we aimed to compare the effects of GSP and GHE delivered by trained LHWs to PLWH presenting with mild to moderate depression in primary care on measures of self-esteem, posttraumatic stress symptoms, social support, stigma, adherence to ART, viral load, number of disability days, asset possession, poverty indices, and cost-effectiveness measures. We hypothesized that compared with PLWH receiving GHE, those receiving GSP will achieve a greater increase in social support and positive coping skills and greater reduction in stigma; larger increases in adherence to ART and greater reduction in viral load; and greater reduction in number of disability days, greater increase in asset possession scores, and larger reductions in poverty index scores at 6, 12, 18, and 24 months after the end of treatment.

We also plan to conduct a process evaluation of trial activities informed by Linnan and Steckler’s process evaluation frameworks [22] to specifically determine indicators of feasibility including *reach* (ie, the proportion of participants who received the intervention), *dose delivered and received* (ie, the amount of intervention delivered and the extent to which participants respond to it), as well as *attrition* (ie, the proportion of participants who are lost to follow-up); indicators of acceptability including satisfaction with intervention content, delivery agents and effects; *fidelity* (ie, whether the intervention is delivered as planned); and causal mediating processes and contextual influences. Given that gender has far-reaching implications for social roles, opportunities, and experience of adversities in traditional societies such as in Uganda [23], we will determine whether or not the effects of GSP are moderated by gender. Both posttraumatic stress [24] and alcohol use disorders [25] are associated with an increased risk for depression. Therefore, we will also examine whether or not the effects of GSP are moderated by psychiatric comorbidities. Extensive reviews of literature [26,27] have found that common factors such as the therapeutic relationship may account for up to nine times greater impact on patient improvement than the specific mechanisms of action found in formal treatment protocols. Therefore, we shall assess whether the strength of a therapeutic relationship will mediate the effects of GSP on depression and subsequently other study outcomes. Identifying groups of individuals for whom GSP works best will assist in the goal of developing selection criteria to guide the referral of patients for GSP.

## Methods

### Study Design

This is a pragmatic two-arm cluster randomized trial evaluating the effectiveness GSP delivered by trained LHWs to persons with HIV presenting with mild to moderate depression in primary care. The study involves LHWs affiliated to 30 primary care health centers (PHCs) in three districts in northern Uganda. Eligible PHCs were randomly assigned (1:1) to have their LHWs trained in the delivery of GSP (intervention) or GHE (control) to PLWH with mild to moderate depression. PLWH treated by trained LHWs will be evaluated at baseline, at the end of intervention, and at intervals of 6 months thereafter for 2 years.

A longitudinal process evaluation of the delivery of GSP by trained LHWs using mixed methods will run alongside the trial to assess acceptability, feasibility, fidelity, and how intervention recipients respond to the different intervention components. Analysis is performed according to the intention-to-treat (ITT) principle and will account for the cluster randomized design. The study protocol is registered in the Pan African Clinical Trials Registry (PACTR201608001738234), and the reporting of the trial will be in accordance with the Standard Protocol Items: Recommendations for Interventional Trials (SPIRIT) guidelines [28] for intervention trials (see Multimedia Appendix 1) and the CONSORT statements for cluster randomized trials [29].

The study was submitted to and approved by both the Makerere University College of Health Sciences Research Ethics Committee and the Uganda National Council of Science and Technology. All study participants will be required to provide written informed consent. Light refreshments will be served during all group sessions in both arms, and every participant will receive a financial incentive to defray transport costs. Figure 1 summarizes the trial profile.

### Study Setting

This trial has been implemented in 30 PHCs situated in three districts in northern Uganda (Gulu, Kitgum, and Pader) with a population of 450,000, 247,000, and 250,000, respectively. Over 90% of the population is engaged in small scale agriculture and animal husbandry as their major income-generating activity. The brutal civil war that the people of these districts endured for two decades (1987-2007) led to a breakdown of health care delivery systems, disorganized social and cultural life with minimal economic activity, and loss of property and infrastructure in these districts. This situation of precariousness led to high poverty rates, risky behaviors including excessive alcohol consumption, and sexual violence making the population highly vulnerable to depression and HIV/AIDS [30].

The first level of health care accessible to this study population is provided by LHWs who work in teams referred to as village health teams. The village health team is affiliated with other PHCs at the second level (Health Center II), third level (Health Center III), or fourth level (Health Center IV), which are led by professional health workers who supervise their outreach activities [31].

**Figure 1 figure1:**
[figure not shown]
Trial flowchart: selection of clusters and participants.

### Participants

#### Cluster Eligibility Criteria, Recruitment, and Randomization

To be eligible for the trial, the primary care health centers had to offer HIV care and treatment services, nominate at least four LHWs (2 men and 2 women) who are actively involved in HIV care, able to read and write, and reside within the villages served by the PHC. PHCs that do not offer HIV care services and those unable to nominate literate LHWs were excluded from the study.

To recruit PHCs, the project team worked with the district health officials in each of the three participating districts and identified a total of 38 PHCs that offered HIV care and treatment services. The health center managers of these centers were informed about the trial and asked to nominate health workers to participate in the trial. The first 10 PHCs in each district that expressed interest in the trial and nominated the required number of health workers were recruited to the trial. The health center managers of the 10 eligible PHCs in each district were invited to a stakeholders’ meeting held at the district’s local government offices with political leaders, district health officials, religious leaders, and community leaders. Study purpose and procedures were explained to facilitate district leadership understanding of the trial activities. At the end of the meeting, the eligible PHCs were randomly allocated with a 1:1 ratio to intervention and control arms. Randomization was done by urn randomization picked by each health center manager or their representative who attended the stakeholders’ meeting.

#### Participant Eligibility Criteria, Recruitment, and Masking

To be eligible for the study, PLWH had to be 19 years and older, diagnosed with major depression assessed with the MINI depression module [32], antidepressant naïve, using ART, and residing in the villages where the trained LHWs lived. Individuals with high suicide risk [33], a severe medical disorder such as pneumonia or active tuberculosis, psychotic symptoms, and hearing or visual impairment were excluded from the study.

On a given clinic day, project research assistants worked with primary care health workers of a participating PHC in the center’s HIV clinic. The primary care health worker gave a health talk on depression to clients in the waiting area. Clients who felt that they had experienced symptoms of depression described in the health talk were invited for further evaluations using the Luo version of the 20-item self-reporting questionnaire [34] and the MINI depression module. This procedure was repeated until a total of 40 PLWH diagnosed with major depression were obtained from a given PHC.

Clients diagnosed with major depression were approached by research assistants who explained study procedures, determined eligibility, and then obtained informed consent. Each client who gave informed consent received baseline assessments with a standardized questionnaire. Recruited participants from the same village were assigned to a trained LHW residing in or near their village to receive the intervention they had been trained to deliver (ie, either GSP or GHE).

By design, both experimental and control interventions were identifiable to participants but will be masked to outcome assessors, the Data and Safety Monitoring Board, and data analysts.

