#### Group Support Psychotherapy Training

Over a 4-month period (January-April 2016), Makerere University in collaboration with the Ministry of Health designed a GSP training program that consists of both formal and informal training. Between May and August 2016, the training-of-trainers model was used to deliver the training, whereby mental health specialists trained PHC health workers who in turn trained the LHWs. Formal training consisted of 8 training modules delivered in a 5-day training workshop that employed active learning techniques including role plays, brainstorming sessions, and small group discussions.

In brief, the first three modules including an overview of the training program, introduction to the GSP model, and introduction to depression and HIV/AIDS were delivered on the first day. On the second and third days, modules on basic counseling skills and effective coping strategies were delivered, respectively. On the fourth day, participants received training in basic livelihood skills (enterprise selection, basic financial skills, and resource mobilization) required to overcome poverty. The last day of training focused on self-care strategies, post-training assessments, and training workshop evaluation. Informal training consisted of conducting supervised pilot GSP sessions. Multimedia Appendix 3 summarizes the competencies targeted by the training.

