#### Group HIV Education Training

In May 2016, Makerere University in collaboration with The AIDS Support Organization (TASO), designed a group HIV education training program that consisted of both formal and informal training. Between May and August 2016, the training-of-trainers model was used to deliver the training, whereby TASO HIV care providers trained PHC health workers who in turn trained the LHWs. Formal training consisted of five training modules delivered in a lecture format in a 2-day training workshop. In brief, on the first day, three modules including an overview of the training program, introduction to depression and HIV/AIDS, HIV progression and transmission were delivered. On the second day, modules on mother-to-child transmission and basic facts on ART were delivered. Informal training consisted of conducting supervised pilot GHE sessions.

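### Patients were identified and consented after open allocation of their health center, a recruitment-bias risk that the planned covariate rule guards against only weakly

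*Protocol article*

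**What the plan says.** All references are to the protocol article.

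- **Allocation** (Cluster Eligibility Criteria, Recruitment, and Randomization): "At the end of the meeting, the eligible PHCs were randomly allocated with a 1:1 ratio to intervention and control arms". The method was open to the centers: "Randomization was done by urn randomization picked by each health center manager or their representative who attended the stakeholders’ meeting".
- **Training by arm, May to August 2016.** In the intervention arm, "mental health specialists trained PHC health workers who in turn trained the LHWs", and "Formal training consisted of 8 training modules delivered in a 5-day training workshop" (Group Support Psychotherapy Training). In the control arm, "TASO HIV care providers trained PHC health workers who in turn trained the LHWs", in a two-day lecture course of five modules (Group HIV Education Training).
- **Finding patients** (Participant Eligibility Criteria, Recruitment, and Masking): eligibility includes "residing in the villages where the trained LHWs lived". On clinic days, "The primary care health worker gave a health talk on depression to clients in the waiting area". Clients who saw themselves in the symptoms described were offered the SRQ-20 and the MINI, and this continued up to 40 diagnosed patients per center. Project research assistants then explained the study, checked eligibility and took consent.
- **Masking** (same section): it is claimed for those who assess outcomes, the safety board and the analysts. Both interventions are identifiable to participants.
- **Analysis** (Statistical Analyses): baseline depression score is a covariate. Other possible confounders, with age, gender and socioeconomic status as examples, enter only if they differ significantly between arms.
- **Limitations**: generalizability to other ethnic groups and the adherence measure are discussed. Recruitment after allocation is not.

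**The concern.** In a cluster trial, randomization balances centers in expectation. It balances the patients inside them only if finding and consenting patients does not depend on the arm. Here the first step toward enrolment is a talk by a health worker of a center that knows its arm, followed by self-identification. If the talk, or the way the study is explained, differs by arm, then the people who come forward or agree may differ in chronicity, motivation or expectation.

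Any such difference would enter both primary comparisons (MINI depression and function score at 6 months). Intention-to-treat analysis, the random effect for center and the planned permutation tests address other problems and would not remove it. Nor would a larger sample.

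**Working it through.** **1. Order of events.**

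| Step | Timing | Arm known to those involved? |
|---|---|---|
| Centers draw allocation | end of stakeholders' meeting | yes, drawn by manager or representative |
| Center workers and lay health workers trained for their arm | May to August 2016 | yes |
| Talk, self-identification, screening, consent | undated; eligibility refers to lay workers already trained | speaker and research assistants not listed as masked |
| Sessions delivered | September to December 2016 | yes |

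Enrolment after allocation is a fair reading of the text. Enrolment after training is probable: it rests on the word trained in the eligibility rule and on the training and delivery dates.

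**2. What each safeguard covers.**

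- The SRQ-20 and MINI confirm a diagnosis in those who come forward. They do not equalize prognosis among diagnosed patients, and they say nothing about those who stayed away.
- Consent by project staff keeps center staff out of that step. Masking of these project staff is not stated.
- The quota of 40 per center equalizes numbers, so unequal screening yield between arms would not show in the enrolled totals.
- The baseline depression covariate removes the part of a selection difference that is expressed in that score. The covariates named for certain do not include baseline function, although function is a primary outcome.
- The significance rule for other confounders can miss a prognostically important imbalance that falls short of significance, and it makes the model depend on the data.
- The process measure of reach counts uptake among eligible participants, so it starts after self-identification.

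**3. The plan's own figure.** Inputs from Sample Size and Power Calculations: p0 = 0.25, p1 = 0.15, k = 0.25, m = 32 per cluster, alpha 5% (sidedness not stated; two-sided reproduces the result), power 80%. With the Hayes–Moulton unmatched formula,

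v = p0(1−p0)/m + p1(1−p1)/m + k²(p0² + p1²) = 0.00586 + 0.00398 + 0.00531 = 0.01516

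c = (1.960 + 0.842)² × 0.01516 / 0.10² = 11.90, rounded up to 12 per arm, with power 0.803.

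This matches Table 2; all eight rows reproduce. The sample size is not at fault. It simply assumes no selection difference between arms.

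**4. Illustration of size (assumed, not from the documents).** Suppose the arms differ by a share g of patients whose 6-month risk is D points lower. The shift in the arm's proportion is g × D: 10% × 10 = 1 point, 20% × 10 = 2, 20% × 15 = 3, 30% × 15 = 4.5. No credit is given here for baseline adjustment.

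Take no true effect, 25% in the control arm, 15 clusters per arm, 32 analysed per cluster and k = 0.25. With no shift, v = 2 × 0.00586 + 0.0625 × 0.125 = 0.01953 and SE = √(0.01953/15) = 0.036. The chance that a nominal 5% two-sided test rejects is Φ(b/SE − 1.96) + Φ(−b/SE − 1.96), with SE recalculated for each shift b:

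| Shift b (points) | 1 | 2 | 3 | 4 | 5 |
|---|---|---|---|---|---|
| 32 per cluster | 5.9% | 8.8% | 13.9% | 21.4% | 31.4% |
| 30.4 per cluster | 5.9% | 8.6% | 13.6% | 20.9% | 30.5% |

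The second row uses the 1140 recruited: 1140/30 = 38 per center, and 38 × 0.8 = 30.4 after 20% loss. The shift could equally run the other way: a true 10-point benefit with a 3-point opposing shift would appear as 7 points.

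**The case against.** The case on the other side is substantial, and much of it stands.

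- **The speaker's training.** A reader might infer that the talk was given by a worker trained for that center's arm. The article says only that a health worker of the participating center gave it. It does not identify the speaker as trained, and it gives no recruitment dates.
- **Overlap of content.** Five days against two suggests very different talks. Yet both curricula contain an introductory module on depression and HIV, which is the part closest to such a talk, and some of the extra intervention-arm time goes to coping, livelihood skills and self-care. An arm-dependent talk is possible, not shown.
- **Existing safeguards.** It would be wrong to say that the baseline comparison is the only protection. The diagnostic gate is the same in both arms, project staff take consent, baseline depression score is in the model, and regular reports cover group comparability.
- **Silence in a condensed article.** A talk script, an arm-neutral explanation and the recruiters' knowledge of allocation may be set out in the full protocol. Their absence here is not counted against the plan. The flowchart (not shown) and the commitment to cluster CONSORT reporting may already supply some screening counts.
- **The numbers are assumed.** Nothing in the documents supports a particular g, D or direction.

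What survives is the sequence itself, the roles listed as masked, the weak rule for further covariates, and a Limitations section that does not mention the risk.

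**Conclusion.** The concern holds as a risk of identification and recruitment bias that the analysis and the stated limitations should address. It is not evidence that bias occurred. A reader might conclude that the trial has lost the protection of randomization. The documents do not support that: center-level characteristics remain protected, and patient-level comparability is at risk, not shown to have failed.

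Size and direction are unknown. The illustrative rise in the 5% error depends wholly on the assumed shift and gives no credit for the adjustment already planned, so it shows only that a shift well below the 10-point design effect could matter. That enrolment followed allocation is a firm reading; that it also followed arm-specific training is a probable one. The point bears on both primary outcomes and should be dealt with, but it does not invalidate the design.

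**What to change.** With 1140 patients enrolled and 6-month assessments done, changes to the talk or its speaker can no longer help this cohort. Three changes remain.

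1. **Statistical Analyses.** Fit both primary outcomes with a fixed set of baseline prognostic covariates, at least as a sensitivity analysis, instead of relying on significance tests to choose them: SRQ-20 score, function score, trauma events, alcohol use, sex and age. All are in the baseline schedule (Table 1, with sex and age under the sociodemographic variables). Because the 6-month analysis is described as in progress, fix and date the set before arm labels are disclosed; otherwise label the analysis post hoc. It cannot correct unmeasured differences.
2. **Reporting.** Tabulate by arm and center, as far as logs exist, how many clients self-identified, screened positive, were eligible and consented. Where logs are missing, say so.
3. **Limitations.** State that patients were identified and consented after open allocation of centers, and that selection differences between arms cannot be excluded.

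The cost is one extra model per primary outcome, one table and one or two sentences, with no new data collection. The price is a candid qualification of the main comparison.
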